### Study Population

The study includes 18- to 25-year-old (inclusive) Australians who identify as having a parent/caregiver with a mental illness and/or substance use concern (they do not have to be living with them). Potential participants will be contacted via telephone to ensure they are capable of providing informed consent and are currently not in distress or crisis (using self-report). They need to have access to a computer, mobile phone, or tablet and regular internet access. Those who reside outside Australia and cannot speak English are ineligible.

### Recruitment and Screening

Participants will volunteer following a response to social media, referral from health professionals, or word of mouth. Those interested in participating will be referred to the study webpage, which provides further information about the intervention. On the webpage participants are invited to confirm their age, contact details, parent’s mental health/substance use status, and emergency contact details. A link is provided to a consent form. Participants then complete all baseline questionnaires and are allocated to the intervention or wait-list control group. Once completed, participants will be contacted via telephone within 2 to 3 weeks by an intervention facilitator.

The telephone call with potential participants serves several purposes. It aims to ascertain participants’ expectations of the intervention and gives them an opportunity to ask any questions or voice any concerns they may have. The call helps to verify that the telephone number they provide is legitimate (important if the telephone number needs to be traced due to concerns regarding safety) and to confirm emergency contact details. During the call, the facilitator will gauge participants’ mental health status, their ability to provide informed consent, and whether the intervention is appropriate for them. They will do this by asking participants to self-report their current distress level (on a scale from 0 being no distress to 10 being high distress). The reference committee decided against using a validated mental health screen to exclude participants on the basis of their mental illness, given the high proportion of young adults who come from these families who have a mental health condition [22]. Nonetheless, it will be made clear to participants that the intervention is not a crisis service. If the facilitator assesses a participant as being in distress or in crisis, he/she will provide a referral to another appropriate service. Participants will also be told, during the call, which group they are in and whether they have any questions about this. Those in the control group will be notified that they are required to complete questionnaires in 7 to 8 weeks and also in 13 to 14 weeks.

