### Allocation/Randomization

After completing baseline data collection, participants will be randomly allocated to 1 of the 2 study groups. Randomization will occur via a random number generator (using Statistical Package for Social Sciences), and participants will be allocated according to the timing (ie, order) of signing up for the study to intervention and control conditions. A permutation block of 70 will be used to ensure equivalence of intervention and control group allocations. The project manager will be responsible for the randomization, and the researchers will be blinded to the allocation of participants to the intervention and control conditions. The random number allocation procedure will occur before the commencement of the study. Participants will be informed about their allocation in the initial telephone call and follow-up email.

Those allocated to the intervention group will be provided with a link to the password-protected intervention. Participants in the control group will be given information about other local and national services they can access, including online and face-to-face services. They will be offered the intervention after those in the intervention group complete the postintervention questionnaires (approximately 12 weeks after randomization).

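### Distress, consent capacity and suitability are checked after allocation, in the call that discloses the arm, so exclusions can differ by arm

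*Protocol article*

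**What the plan says.** The order of events is set out in three sections of the protocol article, and they agree.

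- Recruitment and Screening: "Participants then complete all baseline questionnaires and are allocated to the intervention or wait-list control group". Then: "Once completed, participants will be contacted via telephone within 2 to 3 weeks by an intervention facilitator".
- Allocation/Randomization: "After completing baseline data collection, participants will be randomly allocated to 1 of the 2 study groups". No eligibility step stands between baseline and allocation.
- Study Population, on the conditions for entry: "Potential participants will be contacted via telephone to ensure they are capable of providing informed consent and are currently not in distress or crisis".

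Within the call, Recruitment and Screening says that "the facilitator will gauge participants’ mental health status, their ability to provide informed consent, and whether the intervention is appropriate for them". The basis is a 0 to 10 self-rating of current distress, for which the article gives no cut-off. Someone judged to be in distress or crisis is referred to another service. Allocation/Randomization adds: "Participants will be informed about their allocation in the initial telephone call and follow-up email". The stated blinding covers the researchers and does not mention the facilitator who makes the call. Data Analysis promises an intention-to-treat analysis of all participants.

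**The concern.** Randomisation protects the comparison only if membership of the analysed groups is settled before, or independently of, allocation. Here part of the eligibility decision comes after it. The decision is partly subjective and is made by someone who delivers the intervention and who, in the same conversation, announces the arm. Whether the intervention is appropriate is also a different question for a person about to start than for one who will wait about 12 weeks.

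If some people are screened out at this point and not analysed, and if the threshold differs by arm, the arms will differ in distress for reasons unrelated to treatment. Distress is related to the primary outcomes (well-being, and depression, anxiety and stress). With a target of 70, a handful of people is enough to matter.

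**Working it through.** **Tracing the order.** No figure in the article bears directly on this point, so the check begins with the sequence.

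1. Before allocation: age and the parent's mental health or substance use status are confirmed on the webpage, a consent form is linked, and baseline questionnaires are completed.
2. Allocation: directly after baseline, in order of sign-up, from a random sequence drawn up before the study starts.
3. After allocation, within 2 to 3 weeks: the call, with its checks on consent capacity, distress or crisis, and suitability, and with disclosure of the arm.

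Study Population treats the consent-capacity and distress checks as conditions of entry, and Recruitment and Screening still describes the people being telephoned as prospective participants. Data Analysis includes all participants. The article does not say whether someone allocated at step 2 and referred away at step 3 belongs to that group.

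**Size of the risk, as an illustration.** The exclusion rates, the correlations and the restriction to one arm are assumptions; none is in the article. Scores are standard normal, there is no treatment effect, and the most distressed fraction p at the call is lost from the intervention arm only. The mean call score in that arm falls by D = φ(z)/(1 − p), where z is the upper-p cut point:

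- p = 0.10: D = 0.195, about 3.5 of 35 people
- p = 0.20: D = 0.350, 7 of 35 people

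(35 per arm is 70/2, assuming equal allocation.) Let r_B be the correlation of the call score with baseline and r_P its correlation with posttest. The baseline difference shifts by −r_B·D, the posttest difference by −r_P·D, and the difference in change by (r_B − r_P)·D. A negative shift in distress favours the intervention.

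| r_B | r_P | Baseline, 10% | Posttest, 10% | Change, 10% | Baseline, 20% | Posttest, 20% | Change, 20% |
|---|---|---|---|---|---|---|---|
| 0.5 | 0.5 | −0.098 | −0.098 | 0 | −0.175 | −0.175 | 0 |
| 0.7 | 0.7 | −0.137 | −0.137 | 0 | −0.245 | −0.245 | 0 |
| 0.6 | 0.7 | −0.117 | −0.137 | −0.020 | −0.210 | −0.245 | −0.035 |
| 0.8 | 0.6 | −0.156 | −0.117 | +0.039 | −0.280 | −0.210 | +0.070 |
| 1.0 | 0.5 | −0.195 | −0.098 | +0.098 | −0.350 | −0.175 | +0.175 |

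Entries are products rounded to three decimals. The last row is the case in which the call in effect screens on the baseline score itself. A simulation of the first four rows agreed to within 0.001 SD.

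The raw posttest shift is therefore about 0.10 to 0.25 SD in favour of the intervention. The planned analysis is a time-by-group analysis of variance, of which change from baseline to posttest is one component. That contrast moves by −0.035 to +0.07 SD in the first four rows, and by about +0.10 to +0.175 SD, against the intervention, in the last.

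With 20% lost from the intervention arm and 10% from control, D differs by 0.350 − 0.195 = 0.155. The posttest shift is then 0.155 × 0.5 = 0.08 to 0.155 × 0.7 = 0.11 SD. With equal loss in both arms it is zero.

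**Enrolment so far.** The abstract reports 34 intervention and 30 control participants. If these are the first 64 of a 35:35 block, the last six contain one intervention slot. The chance of a split at least this uneven is 2 × [C(35,6) + 35 × C(35,5)] / C(70,6) = 0.20.

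**The case against.** The strongest reply is that exclusion is never stated. The only consequence given for distress is a referral, with no mention of removal from follow-up or analysis. The article also says the reference committee decided against a validated screen for excluding people on grounds of mental illness, which suggests few exclusions. Intention to treat is promised, and the handling of referred people may be set out in the full protocol, which is not shown. This largely stands. A reader might infer that the article contradicts its own intention-to-treat statement; it does not go that far. It is unclear who counts as a participant. What the reply does not remove is the order itself, which the article fixes: entry conditions are checked after allocation.

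Second, the order of topics within the call is not given, and the account of the assessment precedes the mention of disclosure. That the caller knows the arm while judging is therefore an inference. It is a strong one, because the same person announces the arm in the same call.

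Third, a reader might count withdrawal on hearing of the wait list as part of this problem. The documents do not support that: it is ordinary attrition in an open wait-list trial, and reordering would not prevent it.

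Fourth, a reader might infer from the posttest figures a spurious benefit close to a conventional small effect of 0.2 SD. The planned contrast does not show this; under several of the assumed correlations it is unaffected or moves against the intervention.

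Finally, the main remedy comes late. With 64 of 70 enrolled, reordering reaches at most about six people.

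**Conclusion.** The concern holds as a risk created by the stated sequence. Consent capacity, distress or crisis, and suitability are judged after allocation, in the call that discloses the arm, by an intervention facilitator outside the stated blinding. Other eligibility items are settled beforehand and are not in question.

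No bias is demonstrated. The 34 to 30 split is no evidence of one, since a split at least this uneven has a probability of about 0.20 by chance. Bias requires that people referred away are left out of follow-up or analysis and that this happens unequally by arm; the documents establish neither. If both occurred at the assumed 10% to 20% in one arm only, the raw posttest difference would be off by roughly 0.10 to 0.25 SD. The time-by-group contrast would shift less, or in the other direction, depending on correlations the article does not give. The case for acting is that even the direction of any distortion could not be known from the data as planned, and that preventing it costs little.

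**What to change.** For anyone not yet allocated, complete the telephone eligibility check before the allocation is made or visible to the caller, then randomise, then notify by the follow-up email already planned. No new staff are needed. The small cost is that questions about allocation move from the call to the email or a brief later contact.

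For everyone already allocated (64 by October 2, 2019), state that they are followed up and analysed in the allocated arm whatever the outcome of the call. Report post-allocation exclusions and withdrawals by arm, with reasons. This costs only record-keeping and follow-up effort, and it is the part that still reaches nearly the whole sample.

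Reconcile Study Population, Recruitment and Screening, Allocation/Randomization and Data Analysis so that they agree on when a person becomes a participant and who is in the analysis set. The clinical referral rule need not change.

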### Allocation/Randomization

After completing baseline data collection, participants will be randomly allocated to 1 of the 2 study groups. Randomization will occur via a random number generator (using Statistical Package for Social Sciences), and participants will be allocated according to the timing (ie, order) of signing up for the study to intervention and control conditions. A permutation block of 70 will be used to ensure equivalence of intervention and control group allocations. The project manager will be responsible for the randomization, and the researchers will be blinded to the allocation of participants to the intervention and control conditions. The random number allocation procedure will occur before the commencement of the study. Participants will be informed about their allocation in the initial telephone call and follow-up email.

Those allocated to the intervention group will be provided with a link to the password-protected intervention. Participants in the control group will be given information about other local and national services they can access, including online and face-to-face services. They will be offered the intervention after those in the intervention group complete the postintervention questionnaires (approximately 12 weeks after randomization).

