**Results:**

The impact of mi.spot will be examined at pre, post, and follow-up time periods using analyses of variance on each of the measures outlined above. There will be a within-subjects factor (time) and a between-subjects factor (intervention/control). Data analysis will employ the intention-to-treat principle by including all participants in the analyses. Qualitative interview data will be analyzed using interpretative phenomenological analysis along with respondent validation. The Monash University Human Research Ethics Committee (reference number: 2019-18660-30434) approved the trial on April 17, 2019. As of October 2, 2019, 30 participants were enrolled in the control group and 34 participants were enrolled in the intervention group. Result are expected to be submitted for publication in December 2020.

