## Methods

### Design

This 2-arm parallel randomized controlled trial will compare outcomes at posttest and 6-week follow-up for mi.spot and control participants. The protocol is in accordance with the Consolidated Standards of Reporting Trials of Electronic and Mobile HEalth Applications and onLine TeleHealth checklist. The study was undertaken in 2019. The protocol was registered by the Australian and New Zealand Clinical Trials Register on May 5, 2019. The registration number is ACTRN12619000335190.

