### Assessments

The data collection methods were developed and refined for acceptability from a previous pilot [21]. All participants will complete measures before randomization and at equivalent time frames post intervention and follow-up. Posttest completion will be immediately after the 6-week intervention (approximately 6-8 weeks after the completion of the prequestionnaire), and the follow-up questionnaire will be completed 6 weeks after the posttest. Participants will be sent online survey links and reminders using the REDCap database.

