### Primary Outcome Measures

The primary outcome measures used in this study are as follows:

The Mental Health Continuum short form is an internationally applied and thoroughly validated self-administered rating scale that contains items that measure 3 aspects of well-being: emotional, social, and psychological. Participants are asked the degree to which they have experienced emotional, social, and psychological well-being over the past month. The form includes a 6-point Likert scale from 0=never to 5 every day. Scores on this scale can range from 0 to 70, and higher scores indicate higher levels of well-being [23].The *Depression, Anxiety, and Stress Scale* is an internationally applied and thoroughly validated self-administered rating scale that measures levels of depression, anxiety, and stress. Participants are asked the degree to which they have experienced depression, anxiety, and stress over the past month. A 4-point Likert scale is used from 0 (did not apply to me at all) to 3 (applied to me very much or most of the time) within each of the 3 domains. Normal scores for depression, anxiety, and stress ranged from 0 to 4, 0 to 3, and 0 to 7, respectively, and scores above these ranges indicate mild to extremely severe levels in each domain [24,25].

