## Results

### Data Analysis

The impact of mi.spot on participants will be examined at pre, post, and follow-up time periods using analyses of variance on each of the measures outlined above. There will be a within-subjects factor (time) and a between-subjects factor (intervention/control). Data analysis will employ the intention-to-treat principle by including all participants in the analyses.

Interview data will be analyzed within a qualitative framework using interpretative phenomenological analysis (IPA). IPA is an approach that examines participants’ experiences and meanings of a phenomenon [34], and in this case, the facilitator’s and participants’ experiences of mi.spot. IPA also provides a structure for coding and categorization of data [34] and will be used to develop responses to questions regarding feasibility and acceptability. Before analysis, respondent validation will occur, a process that entails providing participants with a copy of their transcript and an invitation to delete any information they believe may be identifiable and/or modify existing or add any information. A second researcher will independently analyze one third of all transcripts. Rather than a numerical index of agreement, consensus will be reached by discussion and referring back to participants’ transcripts.

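### On the stated weeks, wait-list controls are offered mi.spot before their own follow-up questionnaire, so the follow-up comparison may include partly treated controls

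*Protocol article*

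**What the plan says.** All references are to the protocol article.

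- **Allocation/Randomization**, on the controls: "They will be offered the intervention after those in the intervention group complete the postintervention questionnaires (approximately 12 weeks after randomization".
- **Recruitment and Screening**: controls are told in the telephone call that "they are required to complete questionnaires in 7 to 8 weeks and also in 13 to 14 weeks". The call takes place within 2 to 3 weeks of the baseline questionnaires.
- **Assessments**: "Posttest completion will be immediately after the 6-week intervention (approximately 6-8 weeks after the completion of the prequestionnaire". Follow-up comes 6 weeks after posttest, and the two arms are to be measured at equivalent times.
- **Design**: the trial "will compare outcomes at posttest and 6-week follow-up for mi.spot and control participants".
- **Data Analysis**: "The impact of mi.spot on participants will be examined at pre, post, and follow-up time periods", using analyses of variance with time as the within-subjects factor and arm as the between-subjects factor.
- **Primary Outcome Measures**: both primary scales use a past-month recall period. For the Depression, Anxiety, and Stress Scale: "Participants are asked the degree to which they have experienced depression, anxiety, and stress over the past month".

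**The concern.** A wait-list design gives a randomised comparison at a given time only if controls have not had the intervention by then. Here the release of mi.spot to controls depends on when the other arm finishes its questionnaires and on an approximate week. It does not depend on whether the control has completed the last assessment. That approximate week falls before the controls' stated follow-up.

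If some controls have begun the programme when they complete follow-up, the follow-up contrast compares treated participants with partly treated ones. Because the primary scales ask about the past month, any time after the offer lies inside the period being rated. If mi.spot works, the difference between arms at follow-up would most plausibly shrink, and a sustained effect could be read as one that wore off. The same follow-up data enter the time-by-arm analysis, so the problem is not confined to a side comparison.

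**Working it through.** This is calendar arithmetic on the article's own weeks, with randomisation taken as week 0 because it follows baseline directly.

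**Inputs**
- Offer to controls: about week 12, after the intervention arm's postintervention questionnaires (Allocation/Randomization).
- Control questionnaires: weeks 7–8 and 13–14 (Recruitment and Screening).
- Posttest: weeks 6–8; follow-up 6 weeks later (Assessments).
- Call: within 2–3 weeks of baseline (Recruitment and Screening).
- Programme: 6 weekly sessions (The Intervention).
- Recall: past month, taken here as about 4.3 weeks.

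**Where week 12 comes from.** Posttest is at weeks 6–8, so follow-up is at 6 + 6 = 12 to 8 + 6 = 14. Week 12 therefore does not match posttest. It matches only the lower end of the follow-up window. The named event and the bracketed week agree only if postintervention questionnaires means the 6-week follow-up.

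**Gap between offer and control follow-up** (control follow-up week minus offer week)

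| Reading | Control follow-up | Offer | Gap |
|---|---|---|---|
| Offer at week 12, Recruitment and Screening weeks | 13–14 | 12 | 13 − 12 = 1 to 14 − 12 = 2 weeks |
| Offer at week 12, Assessments weeks | 12–14 | 12 | 12 − 12 = 0 to 14 − 12 = 2 weeks |
| Offer at week 12, the 13–14 weeks counted from a call at weeks 2–3 | 13 + 2 = 15 to 14 + 3 = 17 | 12 | 15 − 12 = 3 to 17 − 12 = 5 weeks |
| Offer after posttest | 13–14 | 6–8 | 13 − 8 = 5 to 14 − 6 = 8 weeks |

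**Room for exposure, if a control started on the day of the offer**
- Gap of 1–2 weeks: at most 1–2 of 6 sessions. Share of recall period: 1/4.3 = 23% to 2/4.3 = 47%. On the Assessments weeks the share is 0% to 47%.
- Gap of 5–8 weeks: 5–6 of 6 sessions. Five weeks exceeds 4.3, so the whole recall period lies after the offer.

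**Is there a safeguard elsewhere in the article?** No section makes a control's own follow-up a condition of the offer. Limitations recognises that controls may seek support elsewhere while waiting, but not that the trial itself may supply the intervention before their last assessment.

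**The case against.** The strongest reply is that the sentence is loose rather than wrong. Its bracketed week fits only the 6-week follow-up. On that reading the offer comes after the intervention arm has finished follow-up, and controls on an equivalent schedule should be at or past theirs. What remains is a rounded 12 against a rounded 13 to 14, and on the Assessments weeks the overlap can be zero. An offer is also not exposure: mi.spot is a facilitated programme with set weekly chats, its features are optional, and no start date is given for controls. Zero sessions before follow-up is compatible with the text. The 5-to-8-week range pairs the ends of two different windows; on one shared schedule the posttest reading gives 6 weeks. Finally, the article condenses a fuller protocol, where release rules may be set out.

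Much of this stands. The week-12 reading is the more coherent one, the posttest figures are conditional, and all the figures are ceilings. What does not stand is that the conflict disappears. On the week-12 reading the trigger is still the other arm's completion, so a control who responds late is unprotected. The controls' own stated weeks fall after the stated offer, and counting them from the call widens the gap. A 6-week gap, if posttest were the trigger, would still span the whole programme. Nor is this detail left to another document: the article states a release rule, and that rule does not fit its own assessment schedule.

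**Conclusion.** The concern holds and should be fixed. As written, controls may be offered mi.spot before a comparison that the design treats as randomised and unexposed. The lead is 1–2 weeks on the controls' stated schedule, 0–2 weeks on the Assessments schedule, 3–5 weeks if the controls' weeks run from the call, and 5–8 weeks if posttest is the trigger.

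This rests on taking randomisation as about the time of baseline and on reading the stated weeks at face value. The size of any bias cannot be derived, because neither uptake nor a start date for controls is given. The direction toward no difference assumes that mi.spot is beneficial. The posttest comparison is unaffected if the offer is at week 12.

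**What to change.** 1. Reword the sentence in Allocation/Randomization so that each control is offered mi.spot only after completing their own 6-week follow-up questionnaire or, if it is not completed, after its window (weeks 13–14) has closed.
2. State that the weeks in Recruitment and Screening, Allocation/Randomization and Assessments run from baseline/randomisation in both arms. If the controls' weeks were meant to run from the call, the window closes as late as week 17 and the release must wait until then.
3. Log the date on which each control is given access.
4. If access has already been given earlier, declare posttest the last randomised comparison and report follow-up as not fully controlled, keeping all control records. Do not drop individual controls by access date, because that selects on an event after randomisation.

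The cost is one sentence, one stated time origin and one date per control. Controls wait about 1–2 weeks beyond the stated week 12 if weeks run from baseline, or 3–5 weeks if they run from the call. Step 4 may apply: the abstract reports that "As of October 2, 2019, 30 participants were enrolled in the control group and 34 participants were enrolled in the intervention group". The article does not say whether any control had been offered access. If some had, the claim of a fully controlled follow-up comparison is given up.
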